### Safety endpoints and other data collection

In addition to the outcome measures described, several prospectively defined safety endpoints will be monitored. These include ITA harvest time, gross ITA injury, sternal fractures, chest tube drainage, need for re-operation for bleeding, as well as superficial or deep sternal wound infections. Information on baseline characteristics, intra-operative variables and post-operative outcomes will also be collected prospectively.

### Statistical analysis and sample size calculations

The patient characteristics will be described using means ± SEM or medians (interquartile range) for normally distributed and skewed data as appropriate. Analysis of all endpoints will be conducted using paired analysis. Continuous variables will be analyzed using 3-way ANOVA, adjusting for stratification and time period variables. Differences in conduit flow (ml/min), length (cm), sternal perfusion (# pixel counts/cm^2^), chest wall pain (VAS score), and area of chest wall dysesthesia (cm^2^) will be analyzed using these methods. In addition, chest wall pain and chest wall dysesthesia will also be dichotomized and analyzed as binary endpoints using McNemar's test. All statistical analyses will be conducted using SAS version 9.1 (SAS Institute, Cary, NC, USA).

For the purpose of sample size calculations, change in ITA flow has been chosen as the primary outcome measure. The reason for this choice is that a) this is a clinically important early endpoint affected by harvesting technique, b) there is some preliminary data available from observational studies evaluating ITA flow, and c) there is a lack of preliminary data regarding other endpoints like chest wall pain and dysesthesia to use for a sample size calculation.

The sample size for this study will be 45 patients i.e. 45 pairs of ITAs. Using direct ITA flow at the second measurement, prior to papaverine application, this study will be powered to detect an absolute difference as low as 8 ml/min between the skeletonized and non-skeletonized ITA flows (30% increase in flow) with the assumption of a mean flow of 26.4 ml/min in the non-skeletonized group[14], at a two-sided alpha level of 0.05 and 90% power. Since the estimate for the standard deviation of the difference between paired samples is not known, the standard deviation between unpaired samples of 16.1 was used to calculate sample size[14]. Since the standard deviation of the difference between paired samples is expected to be less that this value, this likely overestimates the required sample size. There is no anticipated loss to follow-up with respect to the intra-operative ITA flow endpoint.

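### The sample size is called a likely overestimate, but on the ordinary reading of the SD of 16.1 that holds only if the within-patient correlation of the two flows exceeds about 0.5, which the protocol neither states nor supports

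*Protocol article*

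**What the plan says.** All of this stands in the protocol article, under Statistical analysis and sample size calculations.

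- Size: "The sample size for this study will be 45 patients i.e. 45 pairs of ITAs".
- Endpoint on which that number is based: "Using direct ITA flow at the second measurement, prior to papaverine application".
- Target effect, as the protocol words it: "powered to detect an absolute difference as low as 8 ml/min between the skeletonized and non-skeletonized ITA flows (30% increase in flow". The control mean is taken as 26.4 ml/min, and the calculation uses a 5% two-sided test with power of 90%.
- Variability: the protocol concedes that it has no figure for the SD of within-patient differences, and says instead that "the standard deviation between unpaired samples of 16.1 was used to calculate sample size".
- Reason given for regarding this choice as safe: "Since the standard deviation of the difference between paired samples is expected to be less that this value, this likely overestimates the required sample size".

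The section gives no correlation between the two arteries of a patient, no pilot SD of the difference and no sensitivity range.

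**The concern.** A paired calculation needs the SD of the within-patient difference. The protocol enters an SD from unpaired samples and describes the substitution as erring on the safe side. A difference between two measurements carries the variation of both, so pairing must first offset that doubling of the variance before the SD of the difference drops below the SD of a single measurement. The break-even is a correlation of 0.5, not zero.

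What is at stake is the reading of the primary result. The protocol tells readers that the trial probably has power to spare for a gain of 8 ml/min. If the correlation were moderate, power would be below 90%, and a non-significant result would be weaker evidence against a gain of that size than the text suggests. Type I error and the validity of the estimate are not affected.

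**Working it through.** **Inputs**, all from Statistical analysis and sample size calculations: n = 45 pairs; difference δ = 8 ml/min (8/26.4 = 30.3%); SD 16.1; two-sided α = 0.05; power 90%; no loss expected for the intra-operative flow endpoint. The correlation ρ is not given, so it is varied.

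**Step 1: reproduce the stated size.** Enter 16.1 as the SD of the difference.

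- Normal approximation: n = (16.1 × (1.960 + 1.282)/8)² = 42.6, so 43.
- Paired t (noncentral t): 45 pairs give 90.3% power and 44 give 89.6%, so the requirement is exactly 45.
- For comparison, two independent groups with SD 16.1 would need 86 per arm, which does not match.

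The stated 45 is therefore correct arithmetic, with 16.1 used directly as the SD of the paired difference.

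**Step 2: what that assumes.** With the same SD for both techniques,

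SD_diff = SD × √(2(1 − ρ)).

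Setting SD_diff = SD gives 2(1 − ρ) = 1, so ρ = 0.5. The largest SD_diff that still gives 90% power with 45 pairs (paired t) is 16.19, which corresponds to ρ = 1 − 16.19²/(2 × 16.1²) = 0.494.

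**Step 3: power over a range of ρ**, with SD = 16.1 per artery, δ = 8 and the paired t.

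| ρ | SD_diff | Power with 45 pairs | Pairs for 90% |
|---|---|---|---|
| 0 | 22.8 | 63.5% | 88 |
| 0.2 | 20.4 | 73.1% | 71 |
| 0.3 | 19.1 | 78.7% | 62 |
| 0.4 | 17.6 | 84.5% | 54 |
| 0.5 | 16.1 | 90.3% | 45 |
| 0.6 | 14.4 | 95.4% | 37 |
| 0.7 | 12.5 | 98.8% | 28 |

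The difference detectable with 90% power scales with SD_diff as 8 × SD_diff/16.19: 11.3 ml/min at ρ = 0, 9.4 at ρ = 0.3 and 7.1 at ρ = 0.6.

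**Step 4: the other reading of 16.1.** If 16.1 were already the SD of a difference between two independent samples, the per-artery SD would be 16.1/√2 = 11.4. Any positive ρ would then bring SD_diff below 16.1, and the protocol's sentence would be right.

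**The case against.** The strongest defence is that the protocol hedges and discloses. It admits that the SD of the difference is unknown, names the substitute and says only what is expected and likely. Expecting an SD of the difference below 16.1 amounts to expecting ρ above 0.5, and the protocol never claims that any positive correlation would do. This stands in part: the substitution is open. What is missing is the condition that it implies and any basis for believing it.

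The document also gives reasons to expect a positive correlation. Conduit flow ties flow to systemic blood pressure and has both arteries measured at about the same time. The Discussion section on paired, within-patient studies lists patient size, diabetes, hypertension and vasoactive substances as shared within a patient. This makes ρ near zero hard to believe, so the 64% is an outer bound and not a forecast. These reasons are qualitative, however, and do not place ρ above 0.5. Pulling the other way, the primary reading is a 15-second cup collection before papaverine, so spasm from handling is still untreated, and the protocol acknowledges measurement error. How far these lower ρ is not known.

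A reader might also count the anatomic differences between left and right origins, conceded in the Discussion, as lowering ρ. A constant left-right shift does not; moreover, side is stratified and the ANOVA adjusts for it. Only side differences that vary from patient to patient would matter, and the document does not quantify them.

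Finally, one might argue that the SD rises in proportion to the mean, so that the skeletonized side has an SD of about 1.3 × 16.1 = 21 and ρ would have to reach about 0.65. No figure in the document supports such an increase, and the point does not rely on it.

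**Conclusion.** The point stands in a conditional form. On the ordinary reading of 16.1 as the SD of single-artery flows, and with equal SDs for the two techniques, the sample size is an overestimate only if ρ exceeds about 0.5. The protocol neither states nor supports that value. Because 45 is the exact requirement at an SD of the difference of 16.1, the 90% power is not assured to be conservative: it is about 79% at ρ = 0.3 and about 95% at ρ = 0.6.

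A reader might infer that the trial is underpowered, or that the calculation is wrong. The document supports neither. The 45 reproduces, no value of ρ is given, and at ρ = 0.6 only 37 pairs would be needed, so the protocol's sentence would then be true. The reading of 16.1 also rests on a cited source that is not shown. The protocol sets the unpaired SD against the SD of the difference, which favours the ordinary reading, but its wording does not exclude the alternative in Step 4.

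This should be fixed. It is an unsupported justification for a figure on which the trial relies, not an arithmetic error.

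**What to change.** Remove the sentence on overestimation, or qualify it by adding that it requires a within-patient correlation above about 0.5. Say what 16.1 measures in the cited source. Then state the condition and a balanced range, for example:

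*With 45 pairs, power is 90% for a difference of 8 ml/min if the SD of the paired difference is 16.1 ml/min, which corresponds to a within-patient correlation of about 0.5 with equal SDs. Power would be about 64% at a correlation of 0, 79% at 0.3 and 95% at 0.6.*

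Keep the sample size at 45 and report the observed SD of the paired differences with the primary result, so that readers can judge the precision achieved.

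The cost is wording only: no extra patients and no change to the endpoint or analysis. The stated power becomes conditional and somewhat less favourable.

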## Discussion

Although the routine use of the internal thoracic arteries is well established among cardiac surgeons, there is considerable debate regarding the optimal harvesting technique for this conduit. In this paper, we describe the rationale and study protocol, utilizing a paired study design for the evaluation of skeletonized versus non-skeletonized harvest of the internal thoracic artery. The primary outcome measure for this study is intra-operative ITA flow. Additional outcome measures include ITA length, sternal perfusion, and post-operative pain and dysesthesias. The strengths of this study include the assessment of multiple clinically relevant endpoints using an efficient study design with within-patient comparisons.

### Limitations of ITA use

The use of ITAs as bypass conduits has been demonstrated to improve clinical outcomes following coronary artery bypass surgery. However, there are several potential reasons that limit the utilization of the ITA. First, the pre-disposition of the ITAs to post-operative vasospasm and hypoperfusion can potentially be amplified in the presence of vasoactive medications and therefore, there is some reluctance to using these conduits in patients undergoing emergency surgery as well as those with poor left ventricular function. Catastrophic consequences of ITA hypoperfusion, including death and cardiac transplantation, have been reported[4]. Second, there is a concern that ITA harvest may compromise sternal healing. Clinical studies have established the association between bilateral ITA harvest and sternal wound infection, particularly in diabetic patients[18]. Post-operative sternal infection and mediastinitis have severe consequences including increased mortality, prolonged intensive care unit and in-hospital stay, and increased economic burden[7]. The third factor relates to the length of usable conduit available. The distal, post-bifurcation ITA is more prone to vasospasm and its use has been linked to early graft occlusion[5]. Although sequential arterial grafting is a strategy that successfully reduces the amount of conduit needed, one of the limitations to multi-vessel arterial grafting is the length of available conduit[19]. Finally, due to the close proximity of the ITA to cutaneous nerves of the chest wall, its harvest by traditional techniques has been associated with significant persistent pain and sensory chest wall changes, also termed the 'internal thoracic artery syndrome'[9]. Various studies have reproduced the finding of increased post-operative pain in patients undergoing ITA harvest versus sternotomy alone[8,10].

### Proposed benefits of skeletonization

The traditional technique for ITA harvest involves a wide dissection of tissue around the artery (approximately 1 to 2 cm) so as to include the internal thoracic vein and surrounding muscle, fat, pleura and connective tissue as part of the ITA pedicle. On the other hand, skeletonization, which involves the harvest of only the artery, has been reported to result in increased ITA length[12], larger luminal diameter[14], and higher ITA flows[20,21]. These assertions are supported primarily by non-randomized, observational studies, which are prone to bias as well as affected by unmeasured confounders that differ between patients e.g. patient size, gender, use of vasoactive medication, and hemodynamic status. One clinical study has also suggested increased preservation of the sternal blood supply with single skeletonized ITA harvest[17]. Whether this reduction in sternal ischemia leads to a decreased rate of sternal wound infection is unknown. There is a suggestion from observational studies that the incidence of sternal complications in patients undergoing bilateral skeletonized ITA harvest is lower than the currently reported rates for conventional bilateral ITA harvesting[15,22]. Only one observational study to date has examined early post-operative pain with the finding of increased pain in the non-skeletonized group[16]. Thus, there is a lack of conclusive data on the proposed benefits of ITA skeletonization.

### Paired, within-patient studies in surgery

The vast majority of randomized clinical trials utilize a parallel study design to assess treatment differences between groups. The paired study design is efficient because it eliminates the effects of between-patient variability and therefore, significantly reduces the number of patients required to detect a difference in the primary endpoint. This design shares many features of cross-over studies, which are often used to assess effects of medications (e.g. blood pressure lowering medications) that are relatively short acting and being used to treat a disease that is relatively stable over time (e.g. hypertension). In cross-over studies, all patients receive both treatments, and the order in which treatments are administered is randomly assigned. The major concerns with this study design are a) carry over effects i.e. persistence of the effects of the first treatment while the second treatment is being administered, and b) changes in the disease state over the treatment periods. The addition of a washout period between treatments, when no treatment is administered, helps to allay some of this concern[23]. In addition to the two period cross-over design, more complicated cross-over designs that can evaluate multiple treatments have also been proposed[24].

Evaluation of surgical interventions is rarely amenable to a cross-over design. However, occasionally the presence of anatomic symmetry within a patient allows for a within-patient comparison. One of the earliest applications of this type of design in a surgical setting was the use of laser photocoagulation in the eyes of diabetic patients using the untreated eye as controls[25]. Our study design shares a number of features of a cross-over study in that each patient receives both treatments, the order in which treatments are administered is randomized, and the outcomes are assessed according to treatment assignment in a side-specific manner. Although it provides an efficient study design, an important implicit assumption of this design is that the organs that receive the intervention are the same i.e. in this case, that the left and right ITAs are the same, both at the pre-treatment stage and with respect to their response to treatment. Although this assumption seems intuitively reasonable, there are certain anatomic differences between the origins of the left and right ITAs that may question this assumption and this is a limitation of this study design. To address this issue, the randomization scheme will stratify according to side (left versus right) to ensure equivalent numbers in both groups.

Another limitation is the inability to assess the effects of skeletonization on sternal wound infections and other endpoints that are not side-specific. Nevertheless, this design allows for the control of various systemic factors that are identical between the two ITAs. These factors include patient size, the presence of diabetes, hypertension, and other cardiovascular risk factors, the systemic consequences of surgical trauma, systemic endogenous release or exogenous administration of vasoactive substances, and particularly important in our case, the subjective pain experience of each individual in response to surgery. A unique feature of this type of paired study is that the treatments are administered at roughly the same time and therefore, period effects are not expected to play a major role in confounding treatment related differences.

### Summary

Skeletonization of the internal thoracic artery is a new surgical technique that can potentially improve the quality of the ITA as a bypass conduit as well as reduce post-operative morbidity. Although advantages of this technique have been suggested in observational studies, definitive data supporting its benefits is lacking. As such, there is significant variation between surgeons in the harvesting technique employed. As cardiac surgeons strive to enhance the efficacy and minimize the morbidity associated with surgical interventions, this study will provide a valid evaluation of clinically relevant effects of internal thoracic artery skeletonization in improving outcomes following coronary artery bypass surgery.
